### Step 1: identify care coordination objectives

The design team will be led by facilitators in a 1-day exercise to identify care coordination objectives (see Table 2 for examples). Objectives will be defined by design team members in the context of PACTs coordinating care for the three conditions of interest. For each clinical condition, the design team is charged with answering, “what is the PACT trying to accomplish when coordinating care?” Trained facilitators will guide the design team to arrive at three to six objectives that meet six recommended criteria ([23]; see also Additional file 1). Objectives will be compared against these criteria to ensure their utility in subsequent steps.

**Table 2 Tab2:** Sample potential coordination objectives and indicators resulting from ProMES methodology

Objective	Indicator
1. Optimize balance of quality vs. length of life given patient preferences	1. Score on patient preferences/satisfaction survey
	2. Length of life compared to algorithm based on stages of disease
2. Ensure timely screening, delivery, and follow-up of care	3. Mean number of days between date provider orders test and date clerk schedules appointment with the patient
	4. Percent of patients eligible for screening tests who receive them in the specified period.
	5. Percent of patients eligible for diagnostic tests who receive them in the specified period.
3. Ensure care is evidence-based and comprehensive by providing the right expertise mix to care for patient	6. Percent of provider type match per patient problem, i.e., the correct type of provider should be working on a patient for every problem on the patient problem list

Sample objectives and indicators are from a brief pilot ProMES session conducted for care coordination specific to cancer care.

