### Participants

For this phase, we will recruit members of all available PACTs at the four Network 12 study sites. Given our site selection criteria, we estimate each study arm will have an average of approximately 152 members clustered into 28 PACTs. For purposes of informed consent, we will treat all PACT members at a site as study subjects; we are aware that not all PACT members may consent to participate; however, our intervention is an intent-to-treat design, and the unit of analysis is the PACT, not the individual PACT member (our outcome of interest, coordination, is by definition a collective construct). Consequently, as long as at least the provider of a given PACT consents, we will include that PACT’s data in our analyses, taking into consideration the limitations of that PACT’s data.

Optimal design software developed by Raudenbush and colleagues [28] was used to calculate the estimated effect size for varying levels of power for a multilevel cluster randomized trial with repeated measures. With a two-tailed alpha of 0.05 and 6 sites with an average of 10 PACTs per site, an intra-class correlation coefficient for sites of 0.02 (estimated from prior VA data), and approximately 12 repeated assessments, we have 80 % power to detect a medium-to-large effect size (*δ* = 1.13) and 87 % power to detect a large effect (*δ* = 1.25). Pritchard and colleagues’ [19] meta-analysis examining the effectiveness of ProMES as improving productivity found a large overall effect size (*δ* = 1.44); accounting for moderators, effect sizes were as high as 2.21. Thus, we should be able to adequately detect improvements using the proposed number of PACTs.

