### Measures

#### Coordination

Coordination will be assessed using the measures developed in phase 1. In addition, the contingency process enables us to form an overall care coordination composite, defined as the simple sum of the indicators [23]. No weighting or additional transformations are necessary, as nonlinearity and complexities are accounted for in the indicators’ contingencies (i.e., the transformation from raw score to an effectiveness scale).

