#### Care coordination

In addition to the ProMES-developed care coordination measures, we will also monitor existing care coordination measures in the PACT Compass (VA’s dashboard for reporting a variety of quality, safety, and value measures related to PACTs) for each study site. As of this writing, these measures consist of the following: ER/Urgent Care Utilization Rate by Panel, Inpatient Admission Rate, 2-day contact post-discharge ratio, and 7-day contact post-discharge ratio. With both standard measures of care coordination and the ProMES-developed measures of coordination in hand, it will be possible to discern the extent to which the values of these existing measures of care coordination are contingent upon coordination behaviors among PACT members. We will also be able to compare agreement between measures of coordination and standard process measures currently in use.

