### Data analysis

For each objective, we will create composite score of coordination effectiveness, calculated per ProMES recommendations, as the simple sum of all the indicators relevant to that objective. The unit of analysis will be the PACT. We will compare across arms the improvement in coordination effectiveness score over time (baseline vs. performance periods) using growth curve modeling. Coordination effectiveness would be the dependent variable; time point and study arm would be level 1 and 2 predictors, respectively. Each will be modeled separately. A significant, positive main effect of time and study arm will indicate differential improvement across arms over time; an intervention arm slope that is significantly steeper than the control arm indicates support for our hypothesis. In addition to our planned hypothesis test, we also have the opportunity to investigate the extent to which performance on existing care coordination measures is a function of PACT coordination effectiveness. We will conduct separate analyses for each care coordination measure in the PACT Compass. For each, we will test a growth curve model with Compass measure as the dependent variable and time, study arm, and the coordination effectiveness composites as predictors. A significant, positive main effect of coordination effectiveness after accounting for time and study arm would indicate support for the hypothesis that better PACT coordination behaviors is associated with better care coordination outcomes as currently measured by the PACT Compass.

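### The support rule for the PACT Compass hypothesis rests on one coordination effect, but each Compass model as described contains three to six, and nothing says which decides

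*Protocol article*

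**What the plan says.** The Data analysis section of Phase 3 first creates one coordination composite for each objective, as the sum of that objective's indicators. After describing the test of H1, it turns to the PACT Compass measures: "We will conduct separate analyses for each care coordination measure in the PACT Compass". Every such analysis is a growth curve, specified "with Compass measure as the dependent variable and time, study arm, and the coordination effectiveness composites as predictors". The rule that follows asks for one effect, that of coordination effectiveness as such, to be both significant and positive once time and arm are in the model. That result, in the article's words, "would indicate support for the hypothesis that better PACT coordination behaviors is associated with better care coordination outcomes".

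Three other places determine what this means in practice:

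- Measures, Care coordination, lists the Compass measures at the time of writing: "ER/Urgent Care Utilization Rate by Panel, Inpatient Admission Rate, 2-day contact post-discharge ratio, and 7-day contact post-discharge ratio".
- Phase 1, Step 1, sets the number of objectives: "Trained facilitators will guide the design team to arrive at three to six objectives".
- Measures, Coordination, defines a single score across objectives: "the contingency process enables us to form an overall care coordination composite, defined as the simple sum of the indicators". The Compass paragraph does not name this score as the predictor.

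The Compass analysis is introduced as an additional opportunity beyond the planned hypothesis test. H1 is the only hypothesis listed under Objectives.

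**The concern.** The predictor set and the decision rule, in adjacent sentences, do not match. The predictors are composites in the plural. The rule speaks of one effect and one hypothesis. A model with several composites entered together has no single coordination effect. It has one partial coefficient per composite, each conditional on the others.

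The text does not say which coefficient decides, how many must be significant, or what follows when the four measures disagree. A result with one significant positive coefficient, one significant negative coefficient and the rest null could be reported as support or as no support, and both reports would fit the wording. At stake is the claim that better team coordination goes with better results on the measures already in routine use. If the choice is made after the coefficients are seen, that claim has no known error rate.

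**Working it through.** The article gives no error rate for the Compass models, so there is no stated figure to reproduce. The check is a count followed by a conditional error calculation.

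**Inputs**

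- Compass measures: 4 (Measures, Care coordination).
- Per-objective composites: 3 to 6 (Phase 1, Step 1, with one composite per objective from Data analysis).
- Alpha: two-tailed 0.05. This is an assumption for these models. The only statement is in the Phase 3 Participants section, for the power calculation: "With a two-tailed alpha of 0.05 and 6 sites with an average of 10 PACTs per site".
- Rule: significant and positive, so 0.05/2 = 0.025 per coefficient when there is no association.
- Correlations among test statistics: not given, so a range is shown.

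**Count.** 4 × 3 = 12 to 4 × 6 = 24 coefficients. Step 1 also says "For each clinical condition, the design team is charged with answering". If the three-to-six target applied to each of the three conditions, there would be 9 to 18 objectives and 36 to 72 coefficients. That reading is not relied on here.

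**If any one significant positive coefficient were read as support, independent tests.** Chance of at least one = 1 − 0.975^k:

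- k = 12: 1 − 0.975^12 = 0.262
- k = 24: 1 − 0.975^24 = 0.455

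**The same with all statistics equally correlated** (simulated normal statistics, 200,000 draws, cut-off 1.96):

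| Correlation | 12 coefficients | 24 coefficients |
|---|---|---|
| 0.3 | 20% | 31% |
| 0.5 | 16% | 23% |
| 0.7 | 12% | 16% |
| 0.9 | 7% | 8% |

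**Joint entry.** Equal positive correlation is not the natural pattern within one model. If k composites correlate equally at ρ, their partial coefficients correlate at −ρ/(1 + (k − 2)ρ). At ρ = 0.5 this is −0.5/1.5 = −0.33 for three composites and −0.5/3 = −0.17 for six. Combining this with a residual correlation of 0.5 between Compass measures gives, by simulation, 23% (three composites) and 41% (six). The chance of significant coefficients in both directions is then about 8% and 21%. With measures correlated at 0.8, the chance of a false positive coefficient is 17% and 32%.

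**Narrower readings of the rule**

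- Support judged within one measure, any composite counting: 1 − 0.975^3 = 0.073 to 1 − 0.975^6 = 0.141 per measure if independent.
- Overall composite as sole predictor: 0.025 per measure. Across four measures, 1 − 0.975^4 = 0.096 if independent and about 0.08 at correlation 0.5.

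Depending on how the one sentence is read, the chance of a false claim runs from 2.5% for a single measure to 46% for the family.

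**The case against.** The strongest reply is that this is an additional analysis in a condensed article. Multiplicity handling for such analyses is commonly left to an analysis plan, which is not shown here. That stands: the missing alpha adjustment is not a finding. It does not answer the point, because the article does fix a support rule, and that rule refers to an effect its own models do not contain.

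A second reply is that nobody wrote that any one of 12 to 24 coefficients suffices. The singular wording may mean the overall composite, and separate analyses may mean separate conclusions. This also stands in part. The larger percentages are conditional on one reading and are not a property of the plan. But the predictors are named in the plural, so the wording does not settle the matter either way.

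A third reply is that the correlations are guesses and independence is implausible, since 2-day and 7-day contact after discharge overlap. That is fair, and it is why a range is given.

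The rule also says positive, not favourable. If lower is better for emergency or urgent care use and for admissions, a positive coefficient on those two measures would not mean better care. The article does not state the direction. The percentages above describe the positive sign as written.

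A reader might go further and infer that false support is likely, or that the analysis is presented as fully confirmatory at unadjusted alpha. The documents support neither. Under the positive-sign rule none of the 12-to-24 scenarios reaches 50%, no alpha is stated for these models, and the analysis is set apart from the planned test.

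**Conclusion.** The concern holds as a mismatch between the stated models and the stated rule. Four Compass models with three to six composites each give 12 to 24 partial coefficients, while the rule for claiming support needs one effect and does not say which.

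If any one significant positive coefficient were accepted, false support would arise in 26% to 46% of cases with independent tests, 16% to 23% at a common correlation of 0.5, and about 7% to 8% at 0.9. Significant coefficients of opposite sign are also possible. These figures rest on an assumed two-tailed 0.05, on three to six objectives in total, on no true association and on assumed correlations.

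The test of H1 is untouched. What is affected is the association claim, which the article partly marks as secondary but still ends with a statement of support.

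**What to change.** In the Data analysis section of Phase 3, choose one of two wordings.

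- **Keep a support rule.** Make the overall composite from Measures, Coordination, the only coordination predictor that decides support in each Compass model. State the coefficient sign that means better care for each measure, and state support separately for each measure. Report the per-objective coefficients as exploratory estimates with confidence intervals, from a separate model: if each indicator belongs to one objective, the overall composite is the exact sum of the per-objective composites and cannot be entered with them.
- **Drop the support rule.** Call the whole Compass analysis exploratory and delete the sentence that turns a significant coefficient into support for the hypothesis.

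Holm's procedure across the four measures is optional. It is needed only if a single overall claim of support is kept, and the smallest p-value would then be compared with 0.05/4 = 0.0125.

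The cost is wording, with no new data. Trial status describes the team as still preparing for Phase 3, so the change could be made before outcomes are analysed. The downside is that no claim of support can be made for a single objective, and the overall composite answers a broader question than the objective-level coefficients do.

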### Step 3: prioritize indicators by developing contingencies

In the ProMES methodology, contingencies refer to what *level* of performance is acceptable or how much a given level of improvement is valued. Contingencies are represented graphically as a function that shows how much a given performance level on a given indicator contribute to overall effectiveness (in this case PACT coordination effectiveness; see Fig. 2). A contingency function is generated for each indicator. By relating each indicator to overall coordination effectiveness, they are put on the same measuring scale, ranging from −100 to +100. Thus, the various indicators can be directly compared, prioritized, and combined into a single measure. Most importantly, it reflects an explicit statement of relative priority among the different elements of coordination and defines levels of coordination-related performance that are expected and valued by the PACT and the facility.

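### The supplementary PACT Compass analysis reads a positive coefficient as support for all four measures, but for ER/urgent care use and inpatient admissions that sign would ordinarily contradict the hypothesis

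*Protocol article*

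**What the plan says.** The Care coordination part of the Phase 3 Measures section names the existing dashboard measures to be monitored alongside the ProMES measures: "ER/Urgent Care Utilization Rate by Panel, Inpatient Admission Rate, 2-day contact post-discharge ratio, and 7-day contact post-discharge ratio".

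The Data analysis section says "We will conduct separate analyses for each care coordination measure in the PACT Compass". For each one, "we will test a growth curve model with Compass measure as the dependent variable and time, study arm, and the coordination effectiveness composites as predictors". It then says how a result will be read: "A significant, positive main effect of coordination effectiveness after accounting for time and study arm would indicate support for the hypothesis". The same sentence spells out what is being supported: PACTs that coordinate better also do better on the dashboard's existing outcomes.

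On the predictor side, Step 3 of Phase 1 passes every ProMES indicator through a contingency function, after which "they are put on the same measuring scale, ranging from −100 to +100". The note to Fig. 2 places the expected level at zero and the maximum level of the most important indicator at 100. The composites are simple sums of these scores. A higher composite therefore means better coordination.

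**The concern.** One sign rule is applied to outcomes that do not share a favourable direction. More post-discharge contact is better, whereas more ER or urgent care use and more admissions would ordinarily be worse. Neither the Measures section nor the Data analysis section says that the two rates are recoded. The contingency scaling that gives ProMES indicators a common direction is described for those indicators only, not for the Compass measures.

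What is at stake is how two of the four Compass results are interpreted. If the sentence were followed to the letter, a finding that better-coordinated PACTs have significantly more admissions would be labelled support for the hypothesis. A finding of significantly fewer would fall outside the stated condition for support. If the direction were instead settled after the results were known, the interpretation would be open to dispute.

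**Working it through.** The plan gives no figure to reproduce here, because the point concerns the sign of a coefficient. The check is to set the rule against each listed measure.

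**Inputs**
- Outcomes: the four Compass measures (Measures, Care coordination).
- Model: the Compass measure itself is the dependent variable, with "time, study arm, and the coordination effectiveness composites as predictors" (Data analysis).
- Predictor: higher means better (Step 3 and the note to Fig. 2).
- Rule: significant and positive means support, with no exception by measure (Data analysis).
- Assumption: lower is better for the two utilization rates and higher is better for the two contact ratios. The article does not state this.

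**Sign check.** Write the model as Compass measure = (time and arm terms) + β × composite. With the composite scored higher-is-better, the hypothesis implies β > 0 where a higher outcome is better and β < 0 where a lower outcome is better.

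| Compass measure | Better direction (assumed) | Sign implied by hypothesis | Sign in the rule | Agree? |
|---|---|---|---|---|
| ER/urgent care utilization rate | lower | negative | positive | no |
| Inpatient admission rate | lower | negative | positive | no |
| 2-day post-discharge contact ratio | higher | positive | positive | yes |
| 7-day post-discharge contact ratio | higher | positive | positive | yes |

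The rule agrees with the hypothesis for 2 of 4 measures and is reversed for 2 of 4.

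**Illustration of the consequence.** Take a two-sided normal test at 0.05. That level is stated for the power calculation ("With a two-tailed alpha of 0.05 and 6 sites with an average of 10 PACTs per site") and is assumed to carry over to the Compass tests. Let the true β/SE for a utilization rate be −t, so that better coordination lowers the rate. Then

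- P(significant and positive) = 1 − Φ(1.96 + t)
- P(significant and negative) = Φ(t − 1.96)

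| True β/SE (assumed) | Rule as written credits support | Rule with the negative sign credits support |
|---|---|---|
| 0 | 0.025 | 0.025 |
| −1.0 | 0.0015 | 0.17 |
| −2.0 | 0.00004 | 0.52 |
| −2.8 | 0.000001 | 0.80 |

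For example, at t = 2.8, Φ(2.8 − 1.96) = Φ(0.84) ≈ 0.80, and 1 − Φ(4.76) ≈ 0.000001. The β/SE values are illustrative and do not come from the article. The table shows only that, for a measure where lower is better, the written sign almost never credits a true benefit, however well the analysis is powered.

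**The case against.** The strongest reply is that the sentence carries its own correction. It names the hypothesis as one about better outcomes, so positive could be read as favourable, and an analyst who saw more ER use could hardly report it as better. It also says that a positive effect would indicate support, not that a positive sign is required. The coding of the measures may be settled in a fuller plan that is not shown.

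Part of this stands. The intended direction can be recovered from the stated hypothesis, the wording is softer than a requirement, and a sensible analyst would probably notice the conflict. The reading of positive as favourable is not supported, however. Earlier in the same paragraph the word describes the sign of the time and arm effects on the effectiveness score. Nothing signals a change of meaning for outcomes where sign and benefit part company. Nor is this a detail merely left open: the article fixes the sign, and fixes it without regard to the measure.

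Three stronger readings are tempting, and the documents do not support them.

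- **That the arm coefficient is spoiled by conditioning on a mediator.** A reader might infer this because the composites are what the intervention aims to change. But the stated question is how far Compass performance depends on coordination effectiveness. Arm is an adjustment covariate, and the article never interprets its coefficient as an intervention effect on Compass measures.
- **That the plan is wrong to omit an arm comparison on the Compass measures.** No hypothesis claims such an effect. A condensed article also cannot show that no such comparison is planned elsewhere, and the data are to be collected in any case.
- **That the composites must be split into between-PACT and within-PACT parts.** This is an optional refinement and corrects nothing stated wrongly.

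**Conclusion.** The sign rule is wrong as written for two of the four Compass measures, the ER/urgent care utilization rate and the inpatient admission rate. For those two, significant results would be misclassified if the sentence were applied literally. For the two contact ratios the rule is correct.

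This rests on two things: that lower utilization is the favourable direction, which is the ordinary reading but is not stated in the article, and that the rates enter the models uncoded, which is how the text describes them.

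A reader might infer that the trial's main conclusion is at risk. It is not. The Compass models are introduced as an opportunity beyond the planned hypothesis test. H1 is tested on the ProMES composites, for which higher is better throughout. The 2-of-4 count describes how many measures the rule fits; it is not a measure of bias. Severity is minor to moderate.

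**What to change.** In the Data analysis section, replace the single sign rule with a direction for each measure: a significant negative coefficient supports the hypothesis for the ER/urgent care utilization rate and the inpatient admission rate, and a significant positive coefficient supports it for the 2-day and 7-day contact ratios. Equivalently, state that the two rates are reverse-scored before modelling and keep the rule as it is. Because the list of measures is given as of the time of writing, the same sentence should say that any measure added later will have its direction fixed before its data are analysed.

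The cost is one sentence, with no new data and no change to the models. The Trial status section puts the team in phase 2 and preparing for phase 3, so the direction can be fixed before performance-period results exist.

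Optionally, a model with time, arm and time × arm, without the composites, could be fitted to each Compass measure as a supplementary arm comparison on data the study will already hold. Its absence is not an error.
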